## 1.0 Purpose of the study:

We will implement and evaluate a fully electronic health record (EHR)-integrated oncology symptom assessment and management program across NMHC, on patient- and system-level outcomes, for patients receiving treatment with curative intent, non- curative intent or post-treatment survivorship care.

### NU-IMPACT Project Aims

This study will focus on **Aim 2** as described in the grant: ***Evaluate the impact of the program by conducting a hybrid Type I/II effectiveness-implementation trial to evaluate the impact of the enhanced care program (EC: symptom monitoring & self-management intervention), relative to usual care (UC) on patient- and system-level outcomes.***

In the second phase of the study (starting at post-implementation), we will include **Aim 3** as described in the grant: ***Identify facilitators and barriers to implementation and disseminate to other health systems***

We will test the effectiveness of a health care system-wide symptom management intervention, implemented across eight adult hematology/oncology, gynecologic oncology and radiation oncology outpatient clinics at Northwestern Memorial HealthCare Corporation (NMHC). A customized PRO assessment portal, NMPRO, built to work within Epic's MyChart portal and its hyperspace, delivers assessments from the Patient Reported Outcomes Measurement Information System® (PROMIS®), and includes options for custom assessments. This enables routine symptom assessment across the NMHC network, including the eight oncology outpatient clinical practices in this study. Using a clinic-level randomized roll-out implementation trial design, we will further test, using an embedded patient-level randomized controlled clinical trial, the effectiveness of an enhanced care (EC) approach to actively engage and motivate participants, in monitoring and managing their symptoms. The existing NMPRO will constitute usual care (UC), and added patient engagement and activation features, via a tailored, patient web-based tool, will comprise the EC condition. This innovative Type I/II hybrid trial design allows for a within- and between-site evaluation of implementation along with a sufficiently powered group-based comparison to demonstrate effectiveness on individual patient outcomes.

### Diversity Supplement and Aims (Grant # 3UM1CA233035-01S1):

The parent grant (NU IMPACT) has utilized the cPRO symptom monitoring questionnaire that prospectively monitors physical functioning severity with the Patient Reported Outcome Measurement Information System - Physical Function (PROMIS-PF) survey via cPRO.

This sub-study will allow us to: 1) leverage the parent grant to map the development of PFs across different cancer patient populations; 2) develop a learning health systems mechanism to support oncology providers to match the right patient, at the right time, with the right rehabilitation service, in the right location (4Rs Referral System); and 3) obtain stakeholder feedback about implementation and dissemination strategies for multi-level (patient, provider, community, system) prevention, detection, and management of cancer-related PFs and the development of risk stratification models for rehabilitation referral. The results from this supplement will inform

the planned R01 resubmission to the NCI to test the combination of cPRO + 4Rs + pre-hab in a large-scale randomized controlled trial.

Please note: Since the sub-study builds off of the main study. The sub-study will not recruit additional patients for analysis, instead it will utilize the consented patients for analysis.

Since cPRO is already embedded in Epic and results are viewed by our oncology providers, we have uncovered a gap in care regarding physical and functional decline that needs to be addressed. We have partnered with [name] [name] and received additional funding from the NCI to address this gap. [name] research shows that the single biggest barrier to care that can address physical and functional impairment is lack of referral for cancer rehabilitation.

We have developed a clinical decisional support system that will match the right patient, at the right time, with the right rehabilitation service in the right place (4Rs). This system will incorporate a best practice alert that will be triggered in response to PROMIS-PF scores and leverage our vast NM Outpatient Rehabilitation Services clinic network.

**Supplement Aim 3: *Identify realistic implementation, dissemination, and adaptation strategies for future hybrid effectiveness trials of pre-habilitation interventions for different cancer patient populations.*** We will conduct focus groups with key stakeholders (patients, oncology providers,

rehabilitation specialists [PT, OT, ST], clinical administrators, patient service representatives) to learn how to implement, disseminate, and adapt the 4Rs to include risk stratification models, respond to changes in patient and provider behaviors, and different clinical settings (inpatient v. outpatient; academic v. community). This early planning is recommended by the NCI.

## **2.0 Background / Literature Review / Rationale for the study:**

Our Research Center will implement a rigorous EHR-integrated symptom monitoring and management system. Our preliminary data suggest that this will improve symptom control and associated quality of life, healthcare utilization, and cancer treatment delivery. This project addresses a very important problem faced by patients with cancer at all phases of treatment: Symptoms that can be identified and treated early, thus producing better clinical, treatment utilization, and humanistic (patient-reported) outcomes. We approach this problem by addressing two critical barriers to progress. One barrier, the health care delivery system itself, will be addressed by introducing a patient-centered learning health system that pivots on assessment and early management of symptoms. Another barrier, the need of many patients to actively participate in their care, will be addressed with tailored, relevant self-assessment and self-management tools for living a healthy life with cancer. Our success in this project can have local and even national effects.

At the local level, we anticipate that the intervention will help patients obtain better symptom control, and will help the clinical delivery system identify and improve its practices and culture in the service of better care for future patients (i.e., we anticipate true adoption). At the national level, based on our leadership in areas of patient-centered supportive care and patient-reported outcomes, and upon our anticipated results, we expect that there will be other comprehensive cancer centers and regional cancer care programs who seek to adopt the supportive care methods, technologies, and treatments we successfully implement at NMHC. Additionally, with our participation in the IMPACT Consortium, we believe that we in turn will learn from the successes of others in this era of value-based, patient-centered cancer care delivery. The IMPACT project is one of several initiatives funded by the National Cancer Institute (NCI) Cancer Moonshot that are aimed at accelerating a decade's worth of cancer research in five years. As a cooperative grant, three Research Centers and a Coordinating Center work collaboratively to conduct evidence-based research to improve symptom control for cancer patients. IMPACT was designed to accelerate the use of effective symptom management systems that collect patient-reported data and support clinical responses consistent with evidence-based guidelines. As such, each Research Center is implementing their own ePRO interventions. Using implementation science approaches, IMPACT will evaluate the adoption of integrated electronic systems for monitoring and managing patient-reported symptoms in routine cancer care.

In support of the sub-study, physical and functional symptom burden is known to be high among cancer survivors and is an ideal target for chronic care management. Cancer-related physical and functional side effects (PFs) include joint pain, fatigue, muscle weakness, loss of range of motion, altered skin sensation and integrity, postural abnormality, and lymphedema. Cancer survivors lack the knowledge and skills to prevent, detect, and manage PF side effects. Our research shows that a majority of cancer survivors report 3 or more long-lasting PFs and that rehabilitation services are

under-utilized to treat them. Cancer rehabilitation interventions can reduce PFs and support functional ability. However, our work shows that cancer survivors lack receptivity to and misunderstand the benefits of cancer rehabilitation – even among those with cancer-related disability. Oncology providers also lack system support for timely identification of PFs and referral to rehabilitation. Usual cancer care lacks ownership for effective surveillance and management of PFs that can be done without interrupting clinical flow and overburdening providers and patients. Early rehabilitation (pre-hab) could facilitate ownership of PFs by educating patients on early detection and self-management of PFs, but this approach is completely absent from usual cancer care. The parent grant (NU IMPACT) has developed the cPRO symptom monitoring questionnaire that prospectively monitors PFs severity with the Patient Reported Outcome Measurement Information System - Physical Function (PROMIS-PF) survey.

With this sub-study, we will be able to: 1) leverage the parent grant to map the development of PFs across different cancer patient populations; 2) develop a learning health systems mechanism to support oncology providers to match the right patient, at the right time, with the right rehabilitation service, in the right location (4Rs Referral System); and 3) obtain stakeholder feedback about implementation and dissemination strategies for multi-level (patient, provider, community, system) prevention, detection, and management of cancer-related PFs and the development of risk stratification models for rehabilitation referral. The results from this supplement will inform the planned R01 resubmission to the NCI to test the combination of cPRO + 4Rs + pre-hab in a large-scale randomized controlled trial.

### 3.0 Inclusion and Exclusion Criteria:

#### Aim 2

Participants will represent three phases of the cancer treatment continuum:

1. Treatment with curative intent (i.e., as patients receive chemotherapy or biological therapy with curative intent);
2. Treatment with non-curative/palliative intent, including patients with advanced or metastatic disease who receive chemotherapy or biological therapy to control or slow the advancing of their disease, thereby relieving symptoms and/or extending progression-free survival and overall survival; and
3. Cancer survivorship (i.e., patients who have completed active cancer treatment with curative intent and are free of any evidence of disease, including those who are receiving maintenance or prophylactic hormonal or other cancer treatment.

#### INCLUSION CRITERIA:

##### 1. Curative Intent Group:

- ≥ 18 years of age;
- medical chart confirmed diagnosis of a solid or hematological malignancy within the last 10 years;
- had an appointment at a participating site with a participating oncologist in the last year;
- willingness to be randomized (post-implementation only);
- have initiated primary treatment with curative intent within the past 3 months (i.e., as patients receive surgery, standard- or high-dose chemotherapy, biological therapy, and/or radiotherapy);

- provider confirmed planned treatment and follow-up within the Northwestern Medicine hospital and clinics;
  - provider confirmed planned treatment and follow-up within the Northwestern Medicine hospital and clinics; and
  - able to read English or Spanish.
2. Non-Curative/Palliative Intent Group:
- ≥ 18 years of age;
  - medical chart confirmed diagnosis of advanced or metastatic solid or hematological malignancy within the last 10 years;
  - had an appointment at a participating site with a participating oncologist in the last year
  - provider confirmed planned treatment and follow-up within the Northwestern Medicine hospital and clinics;
  - willingness to be randomized (post-implementation only);
  - undergoing cancer treatment with non-curative/palliative intent (e.g., patients with advanced or metastatic disease who receive chemotherapy, biological therapy, and/or radiotherapy to control or slow advance of their disease);
  - provider confirmed planned treatment and follow-up within the Northwestern Medicine hospital and clinics; and
  - able to read English or Spanish.
3. Cancer Survivorship Group:
- ≥ 18 years of age;
  - medical chart confirmed diagnosis of solid or hematological malignancy within the past 10 years;
  - had an appointment at a participating site with a participating oncologist in the last year;
  - provider confirmed planned treatment and follow-up within the Northwestern Medicine hospital and clinics;
  - willingness to be randomized (post-implementation only);
  - completed active cancer treatment with curative intent, including those who may be receiving maintenance or prophylactic cancer treatment;
  - provider confirmed planned cancer follow-up care (with or without treatment) within the Northwestern Medicine hospital and clinics; and
  - able to read English or Spanish.

### Aim 3

- *Clinician Focus Groups*

- Clinical or operational leader in an NM clinic participating in cPRO implementation
- Familiarity with/experience using cPRO for at least 1 year

- *Patient-facing Interviews*

We plan to conduct individual patient interviews with participants from three different cohorts:

- **Cohort 1: Enhanced Care User Group:**
  - Met eligibility criteria for parent study (listed in Inclusion and Exclusion Criteria for Aim 2)
  - Completed NU IMPACT post-implementation study in past 3 months
  - Randomized to the Enhanced Care group in the parent study

- Did not withdraw from the parent study
- Accessed the MyNM Care corner at least once during study participation
- English or Spanish speaking
- **Cohort 2: Enhanced Care non-User Group**
  - Met eligibility criteria for parent study (listed in Inclusion and Exclusion Criteria for Aim 2)
  - Completed NU IMPACT post-implementation study in past 3 months
  - Randomized to the Enhanced Care group in the parent study
  - Did not withdraw from the parent study
  - Never accessed the MyNM Care corner during study participation
  - English or Spanish speaking
- **Cohort 3: Non-Consented**
  - Met eligibility criteria for parent study (listed in Inclusion and Exclusion Criteria for Aim 2)
  - Electronic medical record designation of Hispanic/Latino ethnicity and preferred Spanish language
  - Invited to participate in the NU IMPACT post-implementation study but did not consent

#### Supplement Aim 3:

- *Clinician Focus Groups*
  - Clinical stakeholders include clinicians and/or clinical staff members who have used the 4Rs system in any capacity for the purposes of sending rehabilitation referrals during the pilot.
- *Patient Focus Groups*
  - Consented under parent study
    - Patients enrolled in the parent study (NU IMPACT) and who received a referral to cancer rehabilitation services (PT, OT, ST, and/or PM&R) as a result of their provider having used the 4Rs system during the Supplement pilot.
  - Non-consented under parent study
    - If non-consented patients received a referral to cancer rehabilitation services (PT, OT, ST, and/or PM&R) as a result of the 4Rs system being used as standard clinical workflow, these patients will also be eligible to participate in patient focus groups.
- 

#### **4.0 Sample Size:**

For **Aim 2**, this study will involve voluntary participation of an estimated 12,671 English- and Spanish-speaking participants, with the estimate based upon a 70% acceptance rate and the 2016-

2017 patient volume statistics. Eligibility includes patients receiving treatment with curative intent, treatment with palliative (non-curative) intent, and disease-free survivors. Based on the demographic characteristics of ambulatory oncology patients across six of the eight target clinics (radiation oncology estimates are not included), we anticipate that 13% of our participants will be Hispanic/Latino (hereinafter referred to as Hispanic), 13.3% African American, 4% Asian, and about 69.7% non-Hispanic white. We anticipate that our sex distribution will be about 45% male and 55% female, and that about 40% of our Hispanic participants will either be Spanish monolingual or endorse Spanish as a language of preference.

Based upon 2016-2017 experience, we project an annual volume of over 18,000 unique patients across the six of the eight clinical units, ranging from 1,500-4,500 per unit. We will study implementation of the NMPRO system, including an enhanced care (EC) component as part of a randomized trial, for all adult patients, being treated in all three phases of the cancer treatment continuum. Although there is some cross-unit variability in proportion of patients per treatment phase, we estimate that on average each unit will see 40% of its new patients being treated for cure, 30% will be treated for life extension, and 30% will be disease-free survivors. Based upon our prior experience with very similar studies, we anticipate conservatively that 70% of patients will agree to participate in the study. We also have extensive experience in retention of patients in studies with follow-up out to 1-2 years. Therefore, we anticipate 10% dropout (20% in palliative setting) for this study. Assuming a nine-month enrollment at each site, this will produce the anticipated sample size.

We plan to enroll **12,671 participants** (across 8 clinical sites) for the Type I/II hybrid trial that consists of pre-implementation cohort and post-implementation, randomized cohort to evaluate the implementation of the intervention. For the pre-implementation/non-randomized cohort, we aim to enroll 6,336 participants who will complete additional REDCap ePROs along with the PROMIS CATs and supportive care needs assessment that are part of NMPRO. Participants will be stratified by region, clinical site and cancer treatment continuum phase. Additionally, within each region, intervention roll-out to clinical sites will be randomized.

For the post-implementation randomized trial cohort, again, we aim to enroll 6,336 participants who will be randomized into the usual care (UC) arm or the enhanced care (EC) arm to test the effectiveness of a system-wide symptom management intervention. As in the pre-implementation, the UC arm will complete additional REDCap ePROs along with the PROMIS CATs and supportive care needs survey, called *“Your pre-appointment cancer symptom and needs assessment (cPRO-Monitor)”* questionnaire, that are part of NMPRO, which constitutes usual care. The EC arm will also complete additional REDCap ePROs along with the PROMIS CATs and supportive care needs assessment that are part of NMPRO, as well as receive patient engagement and activation features via a *patient-facing, tailored, web-based tool*. The web-based tool will be called My NM Care Corner. Within each trial arm (approximately 3,168 participants per arm), participants will be stratified by region, clinical site and cancer treatment continuum group.

For our qualitative work in **Aim 3**, we plan to enroll up to 30 clinicians, 10 administrators and 50 patients to explore facilitators and barriers to the implementation of cPRO and patient experiences with the intervention. Each clinician focus group will include 6-12 participants, generally regarded as sufficient for facilitating both individual contributions and group dynamics in a controlled

setting. For patient-facing individual interviews, we plan to recruit 15 patients each across the three cohorts.

For aim 3 of the supplement study, both the clinician and patient facing focus groups will include 6-10 participants.

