## NU IMPACT Statistical Analysis Plan

### 1.0 INTRODUCTION

This Statistical Analysis Plan (SAP) for the Northwestern University IMPACT Research Center (NU IMPACT) study includes all plans for data summary and statistical analyses in support of NU IMPACT primary, secondary and exploratory hypotheses. A summary analysis plan and sample size justification are included in the NU IMPACT Protocol. The SAP is intended to provide a more detailed description of planned analyses. The SAP is not considered part of the protocol. Thus, modifications to the SAP do not require protocol amendments.

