### Effectiveness

Target enrollment in the patient-randomized trial comparing EC v. UC in the post-I phase is approximately 1000 patients. The target enrollment for the patient-randomized component of the trial was based on planned longitudinal modeling of monthly evaluations of 5 PROs for anxiety, depression, fatigue, physical functioning and pain interference. Assuming a compound symmetry covariance structure for the longitudinal measurements with within-subject correlations of 0.5 at all time points, a sample size of 360 is required to achieve 90% power to achieve statistical significance at a Bonferroni-corrected  $p < 0.01$  for an anticipated average difference of 0.3 SD across all time points for EC v. UC. An overall recruitment goal of  $n=1000$  was set to accommodate dropout of up to 64% of patients over time. A Bonferroni correction was used for a conservative estimate of required sample size; for statistical analyses the more powerful step-down Dunnett procedure will be used for p-value adjustment. It is also noted that the target sample size of  $n=1000$  also provides greater than 90% power for detecting a 0.3 SD difference in the FACT G-7 (evaluated at 5 time points) under similar covariance assumptions as the other PROs, as well as simple change-from-baseline differences in PROs from 0 to 12 months using linear models.

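### Protocol and SAP set different sizes (6,336 v. about 1,000) and different dropout rates for the same randomised comparison, and the SAP's 12-month power claim lacks its alpha, model and analysed number

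*Combined protocol and SAP*

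**What the plan says.** **Randomised target.** For the post-implementation cohort, protocol section 4.0 states: "we aim to enroll 6,336 participants who will be randomized into the usual care (UC) arm or the enhanced care (EC) arm". The per-arm figure comes with the stratification: "Within each trial arm (approximately 3,168 participants per arm". SAP section 6.0 (Effectiveness) states: "Target enrollment in the patient-randomized trial comparing EC v. UC in the post-I phase is approximately 1000 patients". Both describe consented patients enrolled after implementation and randomised between EC and UC.

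**Dropout.** Protocol 4.0 anticipates 10%, and 20% in the palliative setting. The SAP's 1,000 "was set to accommodate dropout of up to 64% of patients over time".

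**Justification.** SAP section 1.0 says: "A summary analysis plan and sample size justification are included in the NU IMPACT Protocol". Protocol 4.0 builds its numbers from clinic volume and a 70% acceptance rate. It gives no effect size, alpha or power.

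**The roughly 12,000 patients.** In protocol 4.0, 12,671 is the planned voluntary enrolment across the two cohorts. In SAP 6.0 (Implementation), about 12,000 is the number with electronic health record data, and SAP 7.1 removes patients who consented to the surveys from that dataset. Protocol section 11.0 also describes an implementation cohort of more than 12,000 for which consent waivers are requested.

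**Power.** For a 0.3 SD average difference with compound symmetry and correlation 0.5, SAP 6.0 says "a sample size of 360 is required to achieve 90% power to achieve statistical significance at a Bonferroni-corrected" level of 0.01. It then says that 1,000 patients give more than 90% power for FACT-G7 "as well as simple change-from-baseline differences in PROs from 0 to 12 months using linear models". No alpha, model or analysed number is given for the 12-month claim. SAP 9.1 makes the 12-month comparison a secondary analysis: linear regression on directly observed differences, adjusted for baseline PRO value among other covariates.

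**The concern.** Two current texts give different enrolment targets for one comparison. The SAP states that it is not part of the protocol and can be changed without an amendment, so it does not replace the protocol's figure. Anyone monitoring or reporting the trial could read 1,000 randomised patients either as full recruitment or as 84% short of target (1 − 1,000/6,336).

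The 12-month power statement raises a second question. The target was set at 1,000 because up to 64% may be lost, and month 12 is where cumulative loss is greatest. An analysis of directly observed change excludes patients without a month-12 value. A reader may take a null 12-month result as backed by more than 90% power when that depends on retention, model and alpha.

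**Working it through.** **Inputs.** Effect 0.3 SD, correlation ρ = 0.5, alpha 0.01, 90% power, 1:1 allocation (SAP 6.0 and 3.0). Two-sided testing is an assumption; it reproduces the SAP's figure and one-sided testing does not (312 to 314). For month 12, I also assume 0.3 SD of the raw score, since the SAP does not restate the effect for that clause.

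**1. The SAP's primary figure.** The variance factor for a mean of m measurements is (1 + (m − 1)ρ)/m. With m = 12 it is 6.5/12 = 0.5417.

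n per arm = 2 × (2.5758 + 1.2816)² × 0.5417 / 0.3² = 2 × 14.879 × 0.5417 / 0.09 = 179.1, so 180 per arm and 360 in total. With m = 13 the total is 358. Inflation: 360/(1 − 0.64) = 1,000. Both figures reproduce.

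**2. The two targets.** 6,336/1,000 = 6.3. After each document's own dropout, the protocol keeps 6,336 × 0.9 = 5,702 or 6,336 × 0.8 = 5,069 patients; the SAP's limiting case keeps 360.

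Detectable time-averaged difference (90% power, two-sided 0.01) = 3.8574 × √(4 × 0.5417/N):

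| Basis | N | Difference (SD) |
|---|---|---|
| Protocol, no loss | 6,336 | 0.07 |
| SAP, no loss | 1,000 | 0.18 |
| Protocol, 10% to 20% loss | 5,702 to 5,069 | 0.08 |
| SAP, 64% loss | 360 | 0.30 |

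**3. Power for 12-month change.** The variance of simple change is 2(1 − ρ) = 1, so its SD is 1.0. The baseline-adjusted residual variance is 1 − ρ² = 0.75, so its SD is 0.866. Power = Φ(0.3/(SD × √(2/n)) − z), with n per arm and z = 2.576 (alpha 0.01) or 1.960 (alpha 0.05).

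Example, simple change with n = 180 at alpha 0.01: 0.3/0.1054 = 2.846; 2.846 − 2.576 = 0.270; Φ = 0.607.

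| Observed at month 12 | Simple, 0.01 | Simple, 0.05 | Adjusted, 0.01 | Adjusted, 0.05 |
|---|---|---|---|---|
| 1,000 (no loss) | 98.5% | 99.7% | 99.8% | >99.9% |
| 800 (20% loss) | 95.2% | 98.9% | 99.0% | 99.8% |
| 500 (50% loss) | 78.2% | 91.8% | 90.3% | 97.2% |
| 360 (64% loss) | 60.7% | 81.2% | 76.1% | 90.8% |

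**4. Largest loss from 1,000 that keeps 90% power.** The numbers needed at month 12 are 662 (simple, 0.01), 468 (simple, 0.05), 496 (adjusted, 0.01) and 352 (adjusted, 0.05). The limits are therefore 33.8%, 53.2%, 50.4% and 64.8%.

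**5. Sensitivity to ρ.** With 360 observed at alpha 0.01, moving ρ from 0.3 to 0.7 moves power from 43% to 86% (simple) and from 66% to 92% (adjusted).

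**The case against.** The strongest defence concerns the power claim. The SAP attaches more than 90% to 1,000 patients, and there it reproduces. A reader might infer that the SAP promises this power after 64% loss, or that the figure is an arithmetic error. Neither is supported: the 64% allowance is tied to the primary requirement of 360, and it is a ceiling. The only forecast in the documents is the protocol's 10% to 20%, at which power stays at 95% or higher. Multiplicity adjustment in SAP 9.1 covers the five primary tests, so the secondary 12-month analysis might be tested at 0.05. With the baseline adjustment of SAP 9.1 it would then still have 91% with 360 observed. All of this stands. What remains is that the claim cannot be interpreted without its alpha, model and analysed number.

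A reader might also infer that 12,671 cannot follow from the protocol's inputs, because 18,000 × 9/12 × 0.70 = 9,450 and the protocol says "Assuming a nine-month enrollment at each site, this will produce the anticipated sample size". The documents do not establish that. The volume is given as over 18,000 and covers six of the eight units. Annual counts of unique patients do not scale by 9/12 when patients return for repeat visits. The text does not say whether nine months applies per phase or in total. The target also fits a full year's volume: 12,671/0.70 = 18,101.

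Finally, a reader might conclude that the SAP's target governs and the protocol's should be struck out. The SAP is the only place with a power calculation, but neither document says which target is current.

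None of these answers touches the conflict between the two targets and the two dropout rates.

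**Conclusion.** The sample size is wrong as written in at least one current document: 6,336 and about 1,000 cannot both be the target for the same EC v. UC comparison, and dropout of 10% to 20% cannot be reconciled with planning for up to 64% without explanation. The justification that the SAP attributes to the protocol is not in protocol 4.0. The figure of about 12,000 also needs one definition, because it is used both for consented enrolment and for a records-only cohort.

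The primary comparison is not underpowered by this. Under the SAP's assumptions either size gives at least 90% power for 0.3 SD, including 1,000 with 64% loss.

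The 12-month claim is incomplete rather than false. At full 64% loss, power falls below 90% in three of the four readings, including both at 0.01, the only alpha in the SAP's calculation. It holds for the baseline-adjusted model at 0.05. This rests on ρ = 0.5, 0.3 SD at month 12, two-sided testing and all 64% lacking a month-12 value.

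**What to change.** 1. Reconcile protocol 4.0 and SAP 6.0 to one randomised target, one dropout assumption and one definition of the roughly 12,000 patients (consented enrolment or EHR-only implementation cohort), and explain the change. If the SAP's target is the current one, restate protocol 4.0 as about 1,000 randomised, with 360 evaluable needed for 0.3 SD at alpha 0.01. If the protocol's target is current, the SAP should say so and give its basis.

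2. In SAP 6.0, restate the 12-month claim for the baseline-adjusted model of section 9.1, with its alpha and analysed number. Possible wording: power exceeds 90% if month-12 dropout is at most about 50% (alpha 0.01) or 65% (alpha 0.05); at 64% dropout it is 76% and 91% respectively; for unadjusted change the dropout limits are 34% and 53%. State the assumed correlation and effect size alongside.

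The cost is a protocol amendment, revised SAP wording and a less favourable stated power. No extra patients are needed.
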